### Recruitment Strategy

Participants will be recruited through online advertising on social media platforms (Facebook/Instagram; Meta Platforms, Inc) and via the laboratory website, where a contact email address will be provided for interested individuals to express their interest in participating. Full study information will be sent by email to all interested participants, and informed consent will be obtained via email response before the delivery of the app and the commencement of participation. To minimize information sharing across groups, participants will not have access to one another’s contact or identity details. Additionally, the current version of the app does not allow users to contact other participants or to determine how many others are using the app.

Recruitment is expected to begin in early May 2025 and will continue until the target number of participants in each condition has been reached. Participants may withdraw from the study at any time by contacting the research team via a designated email address provided in the study information form or through a link within the app. All data associated with participants who choose to withdraw will be fully removed from the study and destroyed. Participants will receive financial compensation of €50 (US $56) for taking part in the study.

### Measures

#### Pre-Post and Follow-Up Measures

The following measures will be collected from all participants before/during the intervention, after the intervention, and at follow-up:

The Perseverative Thinking Questionnaire (PTQ) [70], a 15-item self-report measure that assesses the main characteristics of RNT: (1) core features (9 items); (2) unproductiveness (3 items); and (3) capturing mental capacity (3 items). Responses are recorded on a scale from 0 (never) to 4 (almost always). The PTQ has demonstrated good internal consistency and test-retest reliability [70], not only in clinical samples, but also in nonclinical populations and when administered online.

Emotions Beliefs Questionnaire (EBQ), a 16-item self-report questionnaire designed to measure the controllability of emotions and respondents’ beliefs about the usefulness of emotions, which also demonstrates good internal consistency [71]. Respondents answer using a 7-point Likert scale, ranging from “1” (totally disagree) to “7” (totally agree), with higher scores indicating a belief that emotions are uncontrollable or useless.

The Positive and Negative Beliefs About Rumination Scales (PBRS and NBRS, respectively), which comprise 2 scales (positive beliefs: 9 items; negative beliefs: 13 items) that measure metacognitive beliefs related to depressive rumination. Respondents rate the extent to which they agree with each item using a 4-point Likert-type scale, ranging from “1” (do not agree) to “4” (agree very much), with higher scores on each subscale indicating greater positive or negative beliefs, respectively. Both the PBRS and NBRS demonstrate adequate to good internal consistency [72].

Hospital Anxiety and Depression Scale (HADS), a measure of the possible and probable presence of anxiety disorders and depression, comprising 7 items, developed by Zigmond and Snaith [73]. It has been shown to possess good internal consistency, with sensitivity and specificity comparable to the General Health Questionnaire [74]. Respondents rate each item on a scale of 0-3, with higher total scores for each subdomain (anxiety and depression) indicating a greater presence of the disorder. Thresholds for determining the clinical presence of the disorder are as follows: 0-7=normal, 8-10=borderline abnormal (borderline case), and 11-21=abnormal (case).

Cognitive Avoidance Questionnaire (CAQ), developed by Gosselin et al [75], is a 25-item measure of 5 worry-related cognitive avoidance strategies (thought suppression, thought substitution, distraction, avoidance of threatening stimuli, and transformation of images into thoughts), demonstrating good to excellent internal consistency and test-retest reliability [76]. The scale comprises 5 subscales, each containing 5 items that represent individual cognitive avoidance strategies (avoidance of threatening stimuli, distraction, thought substitution, thought suppression, and transformation of images into thoughts). Respondents answer on a 5-point scale (1=not at all applicable to 5=very applicable), with higher scores indicating a greater presence of cognitive avoidance.

The Brief Experiential Avoidance Questionnaire (BEAQ) is a 15-item short version of the Multidimensional Experiential Avoidance Questionnaire, measuring EA content across 6 dimensions. Respondents provide answers to predetermined statements along a 6-point Likert scale (1=strongly disagree to 6=strongly agree), demonstrating good internal consistency and strong convergence with the original Multidimensional Experiential Avoidance Questionnaire dimensions [77].

Additionally, 2 attentional checks are included in the pre-, post-, and follow-up measures. Participants will be explicitly asked to choose a response option (eg, “This is an attentional check; please select the option ‘sometimes’ in response to this question”).

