**Methods:**

Consenting individuals (target N=60) who meet the inclusion criteria (self-reporting problems with repetitive negative thinking) will be randomly assigned to 1 of 4 conditions: (1) intervention with therapist support and daily sampling, (2) intervention without support and with daily sampling, (3) partial intervention (emotion validation EMI only) with daily sampling, or (4) control (daily sampling only). The intervention consists of a series of modules delivered over 4 weeks, with assessments conducted before and after intervention, and again at 1-month follow-up (plus an additional 3-month follow-up for intervention participants). Data will be collected both through online self-report assessments and via the app itself. The potential of the EMI to modify the maladaptive feature of repetitive negative thinking will be assessed using mixed-design ANOVA, while the links between avoidance-mood and rumination-mood, in terms of the moderating effect of trial condition, will be evaluated using multilevel models. These will be assessed as primary outcomes. Secondary outcomes are the effects of a supporting therapist on postintervention outcomes in the intervention groups, and time spent using the app as a measure of engagement (analyzed using the mixed-design analysis of covariance). Compliance will be defined as completing both of the first 2 weeks of intervention content in full, and 5 out of the 6 exercises from weeks 3 and 4. Additionally, the study will control for both the amount of time spent in the app and the length of responses to open-ended questions.

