## Methods

### Study Design

The study takes the form of a 4-arm, parallel-group randomized controlled trial. Total study participation will last approximately 2 months, including preintervention eligibility screening, a 4-week intervention period using the app content and daily sampling, postintervention assessments at the end of the intervention, and a 1-month follow-up period (during which the app will remain available for self-directed use without daily sampling), concluding with follow-up assessments and measurement of any engagement with the app during this period. At this point, control participants will receive the app (minus daily sampling) and guidance on how to use the content. An initial follow-up period of 1 month has been chosen for ethical purposes to minimize the amount of time control participants will wait before receiving the app. For participants in the intervention groups, the study aims to conduct an additional evaluation of outcomes 3 months following the intervention. A graphical summary of the study design is presented in Figure 1.

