**Figure 1 figure1:**
[figure not shown]
Graphical representation of the randomized controlled trial protocol. CBT: cognitive behavioral therapy; RNT: repetitive negative thinking.

Participants will be randomly assigned, using a random-number generator, to 1 of 4 conditions: (1) intervention condition (therapist support); (2) intervention condition (no therapist support); (3) partial intervention (daily sampling and emotion valuation questions); or (4) control group (only daily sampling questions). Active control groups will be utilized to avoid artificially inflating comparisons with intervention condition outcomes [64]. The specific group allocations and the nature of other study conditions will be concealed from participants. Block/random stratification will not be used, as participants will be randomly allocated to 1 of the groups after agreeing to participate in the study. During analysis, demographic characteristics across groups will be compared, and any significant differences identified will be included as control variables.

Therapist support has been shown to improve outcomes in studies of digital mental health interventions [61]. In this study, therapist support will take the form of asynchronous written communication with a cognitive behavioral therapy (CBT) practitioner—either fully qualified or in at least their second year of training—via WhatsApp (Meta Platforms, Inc). This support will be available 2 times a week to relevant participants at specific times predetermined by the therapist. Participants will have the option to utilize this support, but will not be directed to do so. Supporting therapists will be paid at their standard hourly rate for regular patients and will receive an introduction to the app and intervention—while remaining blinded to the full aims of the study—through an online workshop conducted by members of the research team experienced in delivering rumination-focused cognitive behavioral therapy (RFCBT), before the study.

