### Participants and Power Analysis

Participants who self-report problems with RNT will be sought. The first participation in the trial is planned to commence in May 2025. As the study will be conducted remotely and recruitment will continue beyond this date, participants are expected to begin their engagement asynchronously.

To be eligible for the trial, participants must self-report problems with RNT. Participants will be excluded if (1) they are under 18 years of age at the start of the trial; (2) they are currently receiving any form of psychotherapy; or (3) they are currently receiving any form of psychiatric medication. Participants with a psychiatric diagnosis will not be excluded, provided they meet the inclusion criterion and do not meet any of the exclusion criteria listed above.

Sample size was calculated using G*Power version 3.1 [65] for a repeated-measures design with 4 independent conditions measured at 3 time points and assuming a medium effect size. This indicated a required sample size of 60 with equal randomization of participants across groups, which aligns with previous intervention studies in the field [66-68]. As our initial feasibility study during the development of the app content experienced an attrition rate of approximately 60% [69], this study aims to recruit at least double that number to mitigate the risk of significant dropout throughout the trial.

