## Discussion

### Study Strengths and Challenges

This paper outlines the protocol for a randomized controlled trial of an mHealth EMI aimed at reducing EA in the context of rumination. The primary objective of the trial is to investigate whether a reduction in EA through EMI intervention can lead to a decrease in RNT and its maladaptive consequences. Additionally, by implementing the CORTO method, the trial will gather user data on app usability and acceptability, identifying areas for continuous improvement and development.

While the primary objective of this study is to examine the role of EA, we are also collecting data on the use of the app itself. This information will inform its further development and potential efficacy testing in various settings. The app, as it currently stands, and its intervention content have been developed based on our formative user-experience research. While this approach is expected to enhance acceptability, usability, and user retention, and despite the app being thoroughly tested for issues, potential challenges during deployment to real-world users cannot be ruled out. For example, the app currently does not time-lock intervention modules and instead allows users to progress to the next week’s content once the preceding week’s material has been successfully completed. While this approach provides users with flexibility in how they complete the intervention, as recommended by prior studies [92,93], there is a possibility that some users may progress through the content more quickly than intended. This could potentially lead to poor information retention and a diminished impact of the intervention.

Definitions and reporting of compliance can vary significantly across studies of digital interventions [46]. The design of our app enables the remote collection of both daily assessment data and app usage metrics, allowing for precise measurement of engagement and, consequently, intervention compliance. For this study, we have adopted a compliance rate of 80%, consistent with a previous study using EMI and daily assessments with adult populations [89].

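### The Measures section allows the baseline questionnaires to be taken before or during the intervention, which conflicts with the abstract and with their use as the pre-treatment level of the primary ANOVA

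*Protocol article*

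**What the plan says.** **Timing of the first wave.** The Protocol article, Pre-Post and Follow-Up Measures, introduces PTQ, EBQ, PBRS, NBRS, HADS, CAQ and BEAQ with: "The following measures will be collected from all participants before/during the intervention, after the intervention, and at follow-up". The abstract (Methods) describes the same schedule as "assessments conducted before and after intervention, and again at 1-month follow-up". The attention checks, at the end of the same Measures section, are attached to waves labelled pre, post and follow-up.

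**Use of the first wave.** Under Analysis of Trial Outcome Data, Primary Outcomes, the same seven instruments are analysed across pre, post and follow-up by mixed-design ANOVA over all four conditions. The first wave is therefore the baseline level of the time factor.

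**Steps around it.** Study Design describes participation as "including preintervention eligibility screening, a 4-week intervention period using the app content and daily sampling", followed by the later assessments; it names no separate baseline questionnaire step. On eligibility, Participants and Power Analysis says: "To be eligible for the trial, participants must self-report problems with RNT". On allocation, Study Design says "participants will be randomly allocated to 1 of the groups after agreeing to participate in the study". On consent, Recruitment Strategy says "informed consent will be obtained via email response before the delivery of the app and the commencement of participation". Study Strengths and Challenges notes that "the app currently does not time-lock intervention modules".

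**The concern.** The primary ANOVA asks whether change from baseline differs between conditions, so it needs a first score that treatment has not touched. The Measures section gives two permitted times for that score, and one of them falls inside the treatment period.

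A first score given after exposure would absorb part of any effect, and only in the arms that receive content. The control arm has daily sampling alone and would have no such shift. The difference in change between arms then shrinks, so the bias is toward finding no effect.

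The instruments are close to the early content. According to Table 1, Week 1 covers the function of emotions and the avoidance of emotions, which is near to what EBQ and BEAQ measure. Study Objectives also proposes beliefs about emotion and beliefs about rumination as mediators, so a treated baseline on EBQ, PBRS or NBRS would affect those analyses too. A contaminated baseline cannot be recovered once the data are collected.

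**Working it through.** **1. The passages side by side.**

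| Place in the Protocol article | Timing of the first wave |
|---|---|
| Abstract, Methods | before the intervention |
| Pre-Post and Follow-Up Measures, opening sentence | before or during the intervention |
| Same section, attention checks | pre |
| Primary Outcomes | pre |

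The second row cannot be reconciled with the others as written. It is unlikely to refer to daily sampling: the sentence governs the questionnaires listed under it, and daily sampling has its own section (Ecological Momentary Assessment).

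**2. Does another passage close the gap?** Consent must precede app delivery, but no sentence in the article says the same of the questionnaires. Eligibility rests on self-report, so screening yields no scale score that could stand in as baseline. Modules are not time-locked, so the amount of content seen before a late first response is not bounded.

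**3. The plan's own figure.** Participants and Power Analysis gives N = 60 from G*Power for 4 conditions, 3 time points and a medium effect. It does not state alpha, power, the correlation or which term was powered. I assumed f = 0.25, alpha = 0.05, correlation rho = 0.5, sphericity, target power 0.95, and the group-by-time interaction, with k = 4 groups and m = 3 times:

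- lambda = f² × N × m / (1 − rho) = 0.0625 × 60 × 3 / 0.5 = 22.5
- df1 = (k − 1)(m − 1) = 3 × 2 = 6
- df2 = (N − k)(m − 1) = 56 × 2 = 112
- critical F = 2.18, power = 0.954

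The next smaller balanced total, N = 56, gives 0.937, so N = 60 is the smallest that reaches 0.95. The stated figure reproduces under these assumptions. They are not the only set that does: the within-subject factor at rho = 0.3 and power 0.95 also gives 60.

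**4. Illustration of a treated baseline.** Let c be the average share of the effect already present at the first wave in the arms receiving content. If the effect is the same size at post and follow-up, the time profile in those arms changes from (0, δ, δ) to (cδ, δ, δ). Every difference from baseline is multiplied by (1 − c), so f becomes 0.25 × (1 − c). At N = 60:

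| c | f | lambda | power |
|---|---|---|---|
| 0 | 0.250 | 22.50 | 0.954 |
| 12.5% | 0.219 | 17.23 | 0.88 |
| 20% | 0.200 | 14.40 | 0.80 |
| 25% | 0.1875 | 12.66 | 0.74 |

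For scale, c = 12.5% arises if a quarter of participants answer after half the effect has accrued (0.25 × 0.5), and c = 25% if half of them do (0.5 × 0.5). The document gives no basis for any value of c.

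**The case against.** **The rest of the document points to a true baseline.** The section heading, the attention checks, the Primary Outcomes text and the abstract all describe a pre-intervention wave. The feasibility study used pre- and posttests said to mimic this trial. Week 0 of the app only introduces the app and the daily assessments, so the wording could refer to that start-up step. This stands as a reason to think a treated baseline is not intended. It does not remove the conflict, because the looser wording is in the section that defines when these questionnaires are collected.

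**The order of enrolment steps may be given elsewhere.** Figure 1 is not available here, and a journal article leaves such detail to the full protocol. This also stands, and the point does not rest on that silence. It rests on a timing rule that the article states.

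**Stronger readings that are not supported.** A reader might infer that participants are randomised straight after consent and before any baseline. The article says only that allocation follows agreement to participate, in a sentence explaining why stratification is not used. A baseline between consent and allocation, or between allocation and app delivery, is compatible with it. A reader might also infer that participants rate their own baseline knowing their arm. Study Design says that group allocations and the nature of the other conditions are concealed from participants.

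**Conclusion.** The point holds as an internal contradiction about the timing of the primary baseline. One reading, taken literally, would bias the primary condition-by-time effect toward zero. The article permits a treated baseline but does not show that one will occur, so it does not support saying that the trial's baseline is contaminated.

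The direction of the bias follows from the design, provided that the content has an effect. Its size is unknown. The fall in power from 0.954 to between 0.88 and 0.74 depends on the assumed c, on f, rho and alpha values that the article does not state, on reading N = 60 as an interaction calculation, and on an effect of equal size at post and follow-up. It shows that modest contamination would matter; it does not forecast the loss. Nothing here shows that N = 60 is wrong. The correction is worth making because it is nearly free before data collection and impossible afterwards.

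**What to change.** In Pre-Post and Follow-Up Measures, delete the words that allow the first wave during the intervention and state one rule. For example: all baseline questionnaires are submitted after consent and before the app is released to the participant. Use the same rule in the abstract, Study Design and Primary Outcomes.

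Release of the app after submission is enough to remove the treatment contamination. Submission before allocation is preferable as well, since it makes every baseline score and the first attention checks independent of the arm assigned.

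The cost is one sentence and possibly a change in the order of the remote enrolment steps. A few people who do not finish baseline will not enter the trial.

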#### Ecological Momentary Assessment

Users are provided with a daily notification (at a time in the evening of their choosing and for a total of 30 days) to respond to a series of items drawn from existing scales for depression [78], anxiety, well-being, daily goals (and the achievement thereof) [79], emotional experience during the day adapted from Pe et al [80], and RNT [81]. Upon first using the app, users are invited to personalize a time to receive the notification to complete the daily assessment. While a time in the evening is encouraged, flexibility is provided, for example, for individuals working nights. Assessment items can be found in English in Multimedia Appendix 1.

#### User Experience (Contextual, One-Item, Repeated, Timely, Open-Ended [CORTO])

To obtain data regarding the acceptability and usability of the app and to aid its future development, the CORTO (Contextual, One-Item, Repeated, Timely, Open-Ended) method was used, a novel qualitative EMA for obtaining user-experience data in real time [82]. Although originally designed to capture user experiences in relation to games, the method is also relevant in app design as a means of collecting real-time feedback. Data are obtained by presenting users, after each in-app exercise, with 2 closed-ended questions assessing their enjoyment of the app and any difficulties using it, plus 1 open-ended question allowing users to provide detailed, specific feedback on the exercise. Items were amended to replace original instances of “game” with “app” and can be found in English in Multimedia Appendix 2.

#### Additional Control Measures

In addition to the aforesaid measures, data regarding digital health literacy and intervention credibility/expectancy effects will be collected using the eHealth Literacy Scale (eHEALS) and CEQ, respectively [83,84]. The eHEALS assesses respondents’ abilities and skills in sourcing, evaluating, and using electronic health information to address health-related concerns. The scale consists of 8 items measured on a 5-point Likert scale (1=strongly disagree, 7=strongly agree). Total scores range from 8 to 40, with higher scores indicating stronger perceptions of digital literacy in relation to electronic health. The eHEALS-PL demonstrates strong internal consistency (α=.94) [85].

The CEQ consists of 6 items measuring expectations of treatment and the credibility of its rationale in clinical outcome studies. The items are split into 2 sections (“think” and “feel”), with responses for 4 items measured on a Likert scale of 1-9 and for 2 items on an analogue scale from 0% to 100%. Credibility is derived from the first 3 “think” items, and expectancy is derived from the fourth “think” item and the 2 “feel” items. Test-retest reliability is high (expectancy: *r*=0.82; credibility: *r*=0.75; and composite: *r*=0.83) and demonstrates high internal consistency (expectancy: *r*=0.79-0.90; credibility: *r*=0.81-0.86; and composite: *r*=0.84-0.85).

